## Methods

### Research design

Our study is designed as a naturalistic, multi-center prospective cohort study among youth seeking help in addiction treatment to investigate the study objectives mentioned above.

We will recruit youth aged 16 to 22 years (*N* = 420) who enter addiction treatment at ten participating treatment organizations from a total of 13 organizations in the Netherlands. Participants will be assessed on a range of measures related to substance use and SUD, comorbid mental health problems and social functioning at treatment-entry (baseline), end of treatment, and 2 and 4 years post-baseline. Study-inflow of participants consists of consecutive admissions, and will be prestratified by treatment organization to ensure a nationally representative sample. Treatment consists of treatment as usual, as provided by the participating addiction care organizations, to maximize generalizability of the study findings to everyday clinical practice. Analyses will be conducted following an intention-to-treat approach.

This study was funded by The Netherlands Organization for Health Research and Development (60–63,600–98-317) and was approved by the Medical Ethical Board of the Leiden University Medical Center (NL65903.058.18; file number P18.175). Trial registration: NL7928.

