**Fig. 1 Fig1:**
[figure not shown]
Flowchart of the Youth in Transition study

Inclusion criteria are: age 16 to 22 years; primary SUD pertains to cannabis, alcohol, cocaine or amphetamines; willingness to participate in the study (oral and written informed consent). Exclusion criteria are: referral for diagnostic evaluation only; insufficient comprehension of basic Dutch language. The ten participating organizations include specialized addiction treatments and integrated mental health and addiction treatments, with treatment covered by the health insurance system. Recruitment of study participants takes place at 41 treatment locations situated throughout the Netherlands.

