### Treatment

Treatment consists of the usual treatment-offer provided by the addiction care organizations to maximize ecological validity of the study outcomes. We will document the type of treatment received for SUD, which in the Netherlands mostly consists of integrated cognitive behavioral therapy plus motivational interviewing (CBT + MI), community reinforcement approach (CRA), family therapy, and CBT-based e-health interventions. In addition, we will document – psychosocial and/or pharmacological – treatment for comorbid mental health problems as well as intensity (inpatient; outpatient) and actual duration (retention) of treatment, and type of treatment termination (premature/planned).

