We will use existing data from the Tracking Adolescents’ Individual Lives Survey (TRAILS) study to investigate the rate of persistent substance dependence (DSM-IV) and its predictors from adolescence to young adulthood in the general population. TRAILS is a prospective cohort study (*N* = 2230) into the development of mental health from preadolescence (age 11 years) to adulthood (up to age 26 years) in the Dutch general population with five biennial or triennial follow-up waves [58]. Candidate-predictors stem from the areas of: demographic background; substance use and SUD; non-SUD mental disorders; family history; life events; and social functioning (see first six domains in Table 1). Logistic regression will be used to investigate the relation of these predictors with the outcome variable, persistent substance dependence, following the two-step procedure suggested by Hosmer and Lemeshow (2000) [59]. Only variables which are significantly associated with the outcome variable in the first, univariate, step will be entered as candidates into the multivariate (backward) logistic regression model in the second step. Next, we will evaluate the accuracy of the set of combined adolescent risk factors found to predict persistent substance dependence in the TRAILS cohort for predicting persistent DSM-5 moderate to severe SUD among youth in addiction treatment, in terms of sensitivity, specificity, and positive and negative predictive value.
(3)Can we optimize the accuracy of predicting persistent DSM-5 moderate to severe SUD among youth in addiction treatment by extending or modifying the general population-based set of predictors with baseline indicators from our addiction treatment sample?

This question will be addressed (a) by building a new prediction model based upon the same potential predictor variables as used in the TRAILS analysis above, and supplement these with potential predictor variables assessed at baseline in our addiction treatment sample (Table 1), and (b) by comparing the accuracy of this treatment-based prediction model with the TRAILS-population-based prediction model.
(4)Which longitudinal treatment outcome trajectories can be identified from adolescence to young adulthood pertaining to substance use and SUD, comorbid mental health problems, and social functioning among youth in addiction treatment?

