Concerning the fourth study question, we will use the total count of DSM-5 SUD-symptoms derived from the MATE-Y, and the sum score on the DASS-21 (mental health problems) and WHODAS 2.0 (social functioning), assessed at baseline and at two- and four-years follow-up (Table 1). To describe the longitudinal course of SUD, mental health problems and social functioning we will employ latent growth curve modeling [60].
(5)Which treatment interventions – in terms of type, intensity and duration – are associated with favorable or unfavorable long-term outcomes, in terms of substance use and SUD, mental health problems and social functioning, for which youth in addiction treatment?

The fifth study question will be answered in two successive steps. First, we will determine which treatment interventions are associated with a favorable treatment outcome, using the same two-step logistic regression procedure as described for study question 3. Next, we will determine whether the youth-related potential predictors for persistent SUD (see study question 3) moderate the favorable or unfavorable long-term outcomes of the different treatment interventions. To determine which treatment interventions are associated with a favorable long-term – two- and four-years – outcome, we will categorize the treatment received along the following dimensions: type of treatment; intensity; duration; type of termination (see section ‘Treatment’ above).

All study questions will be analyzed using the statistical software packages of SPSS version 25, R, and Mplus, where appropriate.

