## Discussion

This study aims to investigate the long-term course of SUD, concurrent mental health problems and social functioning in a group that is particularly at risk for chronicity: youth in addiction treatment. Strengths of the study are (1) obtaining a nationally representative sample of youth in addiction treatment, (2) the relatively large size of our cohort, (3) the use of both self-report and endophenotypical biological and cognitive-behavioral data, and (4) our aim to determine the long-term outcome of youth addiction treatment in a naturalistic, ‘real world’ treatment context. Study limitations include the following. First, our study sample consists of youth aged 16 to 22 years. We would have preferred to include younger adolescents as well, but Dutch national registration data showed that only 618 youths aged 15 years and younger seek help at addiction treatment annually (i.e., 11% of total youths’ treatment demand). Second, our maximum follow-up period is 4 years. We would have preferred a longer follow-up period (e.g., 8 to 10 years) to sufficiently cover the age of young adulthood, but this was not possible due to budget limitations. Third, our study data are in essence correlational in nature, and hence, are subject to confounding. Including a non-treatment control group would limit confounding, but for reasons of feasibility, ethics and costs, we chose not to include a non-treatment (matched) control cohort in our study. Another option would have been to conduct a large-scale randomized controlled trial (RCT), but for obvious reasons an RCT with a non-treatment control group would be unacceptable for ethical reasons. Nevertheless, we will include important and well-known confounders like social economic status in our analyses. Lastly, most of our data are based on self-report and may be subject to underreporting. Self-reported substance use can be verified by means of urinalyses, but this method only provides a momentary assessment and does not give an indication of amount or severity of use. Studies indicate that self-report is quite reliable if confidentiality is guaranteed and if no negative consequences are attached to the answers provided by the person [61, 62]. To assure that this will be the case, our study assessments will be conducted by research-assistants that are independent from treatment-staff. Nevertheless, youths with insufficient comprehension of basic Dutch language will be barred from the study (exclusion criterion), and hence this potentially important subpopulation will not be represented in our study data.

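### The selection rule applied to study question 5 cannot guarantee that the confounders promised in the Discussion stay in the treatment-outcome models

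*Protocol article*

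**What the plan says.** Under Data analysis, the first step of question 5 is to find which treatment interventions go with a favorable outcome, "using the same two-step logistic regression procedure as described for study question 3". The text under question 3 describes no such procedure; it speaks only of building a new prediction model. The two-step procedure is set out under question 2, for the TRAILS data: "Only variables which are significantly associated with the outcome variable in the first, univariate, step will be entered as candidates" for a multivariable model, which is then reduced backward. No p-value threshold is given and no variable is exempt.

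The Discussion concedes that "our study data are in essence correlational in nature, and hence, are subject to confounding", and offers as mitigation that "we will include important and well-known confounders like social economic status in our analyses".

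Power considerations names question 5 among the logistic analyses and sets a maximum of 12 predictors.

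On organization, Research design says that inflow "will be prestratified by treatment organization to ensure a nationally representative sample". Participants and setting adds that "The ten participating organizations include specialized addiction treatments and integrated mental health and addiction treatments". The Treatment section says: "Treatment consists of the usual treatment-offer provided by the addiction care organizations". The Data analysis section does not mention organization.

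**The concern.** Questions 2 and 3 are about prediction, where choosing variables from the data is at least arguable. Question 5 is different: it asks how treatment type, intensity and duration relate to outcome when nobody assigned the treatment. A confounder matters there through its links to both treatment and outcome. Its own p-value against the outcome does not measure that. The screen is least reliable when a risk factor raises the use of a beneficial treatment, because the two effects then mask each other in the univariate test.

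If the written rule is followed, socioeconomic status or baseline severity leaves the model whenever its p-value is too large. The reported treatment association is then not adjusted for it, although the Discussion tells readers that such factors are included. What is at stake is the plan's one stated analytic safeguard against confounding in question 5.

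**Working it through.** **The plan's own figure.** The predictor limit reproduces: 420 × 0.30 / 10 = 12.6, rounded down to 12. The point does not rest on an arithmetic error.

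**Chance that a real confounder fails the first step.** From the article: N = 420 and a 30% rate. That rate is stated for persistent SUD and is assumed here for the question 5 outcome. Also assumed: the screening threshold, the odds ratios and a 0.5 SD imbalance between treatment groups.

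- SE(log OR) = 1/√(N × 0.3 × 0.7 × var x). For a variable in SD units this is 1/√(420 × 0.21) = 0.1065. For a 50/50 binary factor, var x = 0.25 and the SE is 0.213.
- z = ln(OR)/SE. P(dropped) = Φ(c − z), with c = 1.960 at p<0.05 and 1.150 at p<0.25.
- Approximate distortion of the treatment OR if the confounder is omitted = exp(0.5 × ln OR per SD). The binary factor has ln OR per SD = 0.5 × ln 1.5.

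| Confounder | z | Dropped, p<0.05 | Dropped, p<0.25 | Distortion if omitted |
|---|---|---|---|---|
| OR 1.2 per SD | 1.71 | 60% | 29% | 1.10 |
| OR 1.3 per SD | 2.46 | 31% | 9% | 1.14 |
| Binary 50/50, OR 1.5 | 1.90 | 52% | 23% | 1.11 |
| OR 1.5 per SD | 3.81 | 3% | under 1% | 1.22 |

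If 25% were lost to follow-up (an assumption, N = 315), the p<0.05 column would read 68%, 43%, 62% and 9%. A two-proportion power calculation for the binary factor gives 53% at N = 420, in agreement. Backward elimination can only add to these losses.

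**Masking.** In simulations (1,500 runs per setting, p<0.05 at both steps), a binary confounder with OR 1.5 also raised the odds of receiving a beneficial treatment (treatment OR 0.6).

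- With confounder–treatment OR 2 and 3, the confounder failed the screen in 70% and 77% of runs.
- Treatment survived the two steps in 53% and 44% of runs. With the confounder forced in, it was significant in 64% and 60%.
- With no true treatment effect, the two-step route kept treatment in 4–5% of runs, no more often than the forced model.

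**Organization.** Simulated with 10 organizations of 42 youths, no treatment effect, and an assumed ICC and treatment mix:

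- Where the mix does not vary between organizations, ignoring organization leaves type I error at about 0.05.
- Where it varies strongly (SD 2 on the logit scale), type I error is 0.08 at ICC 0.02 and 0.11 at ICC 0.05.
- With organization in the model it is about 0.05.

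**The case against.** The strongest reply is that the passages can be read together. Question 5 may screen only the treatment variables, with confounders entered alongside, and the article asks only about association and discloses confounding openly. The screening rule is written for candidate predictors in TRAILS and reaches question 5 through an imprecise cross-reference. This stands in part: a reader might infer a flat contradiction, but the documents support only that the written rule does not secure the promise. The reply does not remove the point, because the article fixes a procedure for question 5, describes it once, and exempts nothing.

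Three stronger readings are also tempting and are not supported.

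- **Frequent dropping together with large bias.** The confounder that distorts the treatment OR by 1.22 fails a p<0.05 screen only about 3% of the time. Those dropped often distort it by about 1.10 to 1.14.
- **Harmless treatment commonly declared harmful.** That sicker youths receive more intensive care is a reasonable expectation, not a documented fact. The simulations with one confounder and no treatment effect showed no excess of false findings.
- **Standard errors badly wrong through clustering.** The design effect 1 + 41 × ICC is 1.82 to 3.05 for an assumed ICC of 0.02 to 0.05, so naive standard errors would be 26% to 43% too small (1 − 1/√1.82 and 1 − 1/√3.05). That holds only if everyone within an organization received the same treatment, whereas the article classifies the treatment that each youth received. The article gives representativeness as the purpose of prestratification, and a condensed article may leave site terms to a fuller plan.

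**Conclusion.** The point holds for question 5 only. The rule the article applies there can remove the confounders that its Discussion relies on, and it uses a criterion unsuited to confounders. The effect is moderate: under p<0.05, confounders of OR 1.2 to 1.3 per SD are lost in 31% to 60% of samples at N = 420, with a distortion of about 1.10 to 1.14 for each one omitted; several could accumulate. A strong confounder would usually survive, and a looser threshold reduces the problem without removing it. All these sizes rest on the assumed threshold, effect sizes, imbalance and outcome rate. Organization is a secondary matter: that it shapes treatment type is an inference from the settings described, and the effect of leaving it out may be small.

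**What to change.** Keep data-driven selection for questions 2 and 3. For question 5, state that a short prespecified confounder set is forced into every model whatever its p-value, and correct the cross-reference so that it points to where the procedure is written.

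A workable set, all measured at baseline according to Table 1, is SUD symptom count, primary substance, DASS-21, age, sex, socioeconomic status and prior treatment. With four primary substances (three parameters) and one parameter for each other item, that is 3 + 6 = 9, leaving 12 − 9 = 3 for treatment terms. Models may therefore have to take one treatment dimension at a time, or the set must be trimmed. A propensity score for treatment category is the alternative that keeps the parameter count low. The limit should be recomputed from the events actually observed: at an assumed N = 315 it is 315 × 0.30 / 10 = 9.45, so 9.

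As a secondary addition, include a random intercept for organization, which costs one variance parameter. Nine organization dummies would bring the count to 9 + 9 = 18 before any treatment term, above the plan's limit. The benefit depends on between-organization variation that the article does not give.

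The cost is analysis-plan wording and some model degrees of freedom; no new data are needed.

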### Power considerations

Using a sampling fraction of 10% to obtain a representative sample from the total target population (*N* = 4169; see ‘Participants and setting’ above), we aim to include 420 youth in our study. Concerning our first study question, we assume a 30% persistence rate of moderate to severe SUD in our study sample [20, 21, 52]. With precision at 5% [53], a minimum sample size of *N* = 300 would be sufficient to estimate the assumed 30% persistence rate with a 95% level of confidence [54].

However, for our prediction analyses of persistent SUD (study questions 2, 3 and 5) we need a larger sample size than N = 300 to allow a sufficiently large number of predictor variables to be included in the logistic regression models. To avoid overfit of a logistic regression model, authors recommend a minimum of 10 events (i.e., 10 patients with persistent SUD) for each predictor variable [55–57]. Hence, given the assumed 30% persistence rate, and *N* = 420, a maximum of 12 predictor variables could be included in the multivariate logistic regression analysis.

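### The 12-predictor sizing argument names question 5 but does not extend to that question's moderation step, where an unrestricted, unadjusted search is likely to yield chance moderators

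*Protocol article*

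**What the plan says.** The Study objectives section lists question 5 among the primary questions. It asks which interventions go with good or poor long-term outcomes, and for which youth.

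The Power considerations section treats three questions together: "for our prediction analyses of persistent SUD (study questions 2, 3 and 5) we need a larger sample size than N = 300". The support is a minimum of 10 events per predictor variable, from which it concludes that "a maximum of 12 predictor variables could be included in the multivariate logistic regression analysis". Interaction terms are not mentioned.

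The Data analysis section answers question 5 in two steps. The first relates treatment to outcome with the two-step logistic procedure. In the second, "we will determine whether the youth-related potential predictors for persistent SUD (see study question 3) moderate the favorable or unfavorable long-term outcomes". On the treatment side, "we will categorize the treatment received along the following dimensions: type of treatment; intensity; duration; type of termination". The second step carries no limit on the number of moderators and no exploratory label.

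**The concern.** A count of events per predictor says how many terms a logistic model can hold. Moderation needs at least one product term for every moderator-by-treatment pair, so the number of terms grows as a product of the two lists. The sizing argument is stated for question 5 as a whole, but its second half uses up the allowance almost at once.

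At stake is the reading of any finding on which treatment suits which youth. A reader could take such a finding as coming from an analysis that the sample size was meant to serve. In an open search, some apparent moderators are likely to be chance, and real ones of moderate size would mostly be missed.

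**Working it through.** **Inputs from the article.** N = 420; persistence rate 30% ("we assume a 30% persistence rate of moderate to severe SUD in our study sample"); 10 events per predictor; four treatment dimensions; four main treatment types named in the Treatment section.

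**Assumed, because not stated.** 6 or 12 moderators; two-sided 5% per test, unadjusted; independent tests. Intensity, duration and type of termination take one parameter each. Treatment type takes one parameter, or three if its four named categories are kept.

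**1. The article's own figure.** 420 × 0.30 = 126 events; 126 / 10 = 12.6, so 12 predictors. It reproduces. At N = 300 the same rule gives 90 / 10 = 9.

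**2. Moderators that fit within the 12.** With t treatment parameters and k moderators, a joint model has t + k + t·k parameters.
- t = 4: 4 + k + 4k ≤ 12. k = 1 gives 9 and fits; k = 2 gives 14 and does not.
- t = 6: 6 + k + 6k ≤ 12. k = 1 already gives 13, so none fits.

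With t = 4 and k = 1 the model needs 9 parameters, which N = 300 also allows. On this reading the step from 300 to 420 adds no moderator.

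**3. Hypothetical upper case: 12 moderators in one joint model.**
- t = 4: 12 + 4 + 48 = 64 parameters; 126 / 64 = 2.0 events each.
- t = 6: 12 + 6 + 72 = 90 parameters; 126 / 90 = 1.4 events each.

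**4. Product terms tested one at a time.** If no moderation exists, m tests give 0.05·m expected false moderators, and the chance of at least one is 1 − 0.95^m, per outcome.

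| Moderators | Treatment parameters | m | Expected false | Chance of at least one |
|---|---|---|---|---|
| 6 | 1 | 6 | 0.3 | 26% |
| 6 | 4 | 24 | 1.2 | 71% |
| 6 | 6 | 36 | 1.8 | 84% |
| 12 | 4 | 48 | 2.4 | 91% |
| 12 | 6 | 72 | 3.6 | 98% |

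Tests that share predictors and treatments are not strictly independent. A simulation of the 48-test case (300 data sets, N = 420, no true moderation) gave a mean of 2.5 false moderators and at least one in 91% of data sets, so the approximation is adequate there.

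**5. Power, as an illustration.** Assume binary treatment and moderator, both split 50/50, a 30% event rate in every cell, no loss to follow-up, and a Wald test.
- Main effect, odds ratio 2: SE = √(4 / (420 × 0.21)) = 0.213; power about 90%.
- Interaction, ratio of odds ratios 2: SE = √(16 / (420 × 0.21)) = 0.426; power about 37%.

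The smallest interaction detectable with 80% power is a ratio of odds ratios of 3.3. With 20%/20% splits it is 6.5, and power for a ratio of 2 falls to 18%.

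**The case against.** The best reply is that the power section sets a cap and makes no promise about moderation. It speaks of predictor variables, and a product term can be counted as one. Nor does the analysis section say that all products enter one model. The joint models of 64 and 90 parameters are therefore not the protocol's; they exceed its cap before any product is added (12 + 4 = 16, or 12 + 6 = 18). A model with one treatment variable, one moderator and their product has 3 parameters and 126 / 3 = 42 events each, well within the rule. All of this stands, so those models serve only as an upper bound.

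It is also fair that this is a condensed article. A moderator list, an alpha level and multiplicity control may sit in an analysis plan that is not shown, so their absence is not the fault here. The two-step significance selection is attached only to the first step of question 5, and a reader should not assume that it governs the second.

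A reader might also infer that 420 was chosen to cover moderation. The documents do not support that. The number comes from elsewhere ("Using a sampling fraction of 10% to obtain a representative sample from the total target population"): 0.10 × 4169 = 416.9. The events rule supports going beyond 300. Finally, the article claims no power for moderation, so the 37% contradicts no stated figure.

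The reply does not remove the mismatch. Counting products within the 12 leaves room for one moderator or none. Testing pairs singly respects the cap but leaves the multiplicity and the low power. A separate analysis plan could restrict the tests, but it would not correct the article's sizing statement for question 5.

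**Conclusion.** The point holds in limited form. The arithmetic behind the 12 predictors is correct, and the concern takes the 30% rate and complete follow-up as given. What fails is the extension of that argument to the second step of question 5.

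It is tempting to conclude that this step will certainly produce chance moderators. The article does not support that, because it states neither alpha nor the number of tests. Under unadjusted 5% testing the chance per outcome is about 26% for a narrow search, 71% to 84% for 6 moderators over all dimensions, and 91% to 98% for 12. As written, the step covers all the potential predictors from question 3 and four dimensions, which points to the upper part of that range. The moderator counts, coding, alpha and independence are assumptions. The 126 events apply to persistent SUD only; question 5 also covers mental health and social functioning, where the 30% rate need not apply.

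**What to change.** In Power considerations, limit the 12-predictor statement for question 5 to its first step, and say that N = 420 was not sized for moderation.

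In Data analysis, for the second step of question 5:
- label it exploratory;
- restrict it to a short list of moderator-by-treatment pairs fixed before follow-up data are seen, and count product terms against the same event budget;
- apply a multiplicity adjustment, for example Holm over one joint interaction test per treatment dimension;
- report estimates with confidence intervals.

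The cost is a few sentences and an agreed list; no extra participants or data are needed. The downside is that fewer moderators are examined and the claim for this step becomes weaker.
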